## Statistical methods

### Randomization

Following consent, participants will be assigned a unique confidential study number. They will then be randomly assigned to the three intervention groups using R [25]. We will use permuted block randomization for the following 4 groups: young women and young men (age 65-74), and old women and old men (age 75+).

### Sample size and power analysis

Statistical power was calculated using G * Power [26]. Based on the analysis, 100 participants in each of the 3 treatment groups (experimental, active control, control) enable detecting group differences in statistical power of 86% for a small effect size (Cohen’s f = .15), and in statistical power of 99% for a moderate and high effect sizes (Cohen’s f = .25, .40 respectively). In addition, the statistical power for detecting differences between repeated measures, and in the interaction between groups in the repeated measures is higher than 99% in the moderate effect size as well as in the high effect size.

#### Data analysis

The following 2-ways ANOVAs with repeated measures (3 treatment groups X 4 times measurements – T1-T4) will be conducted for each digital marker as follows:For all participantsSeparately for each of the following four subgroups: young women and young men (age 65-74), and old women and old men (age 75+).Separately for each of the two levels of fitness (Low and High) for each component. For example: low level of balance performance in the experimental group (personalized) compared to low level of balance in the control groups.Bonferroni will be used for post-hoc analyses, and False Discovery Rate [27] will be used to account for multiple comparisons.

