Having successfully completed the pilot study, we present the protocol for the next study stage, which plans to conduct a prospective randomized controlled trial using the study tool among healthy older people. Specifically, the study objectives are to investigate the effectiveness of a remotely delivered personalized 8-week multicomponent exercise program based upon remote individual fitness assessment, compared either to the updated WHO guidelines (active-control) or to no intervention (control). We hypothesize that participants in the personalized experimental group will show greatest motor improvement in balance, strength, and flexibility than participants with similar baseline fitness profiles in the active-control, with least changes observed among the control group.

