### Intervention

As shown in in the study flow chart (Fig. 1), the intervention will last 8 weeks. Following informed consent forms and collection of preliminary demographic and clinical data (T0), all participants will undergo fitness assessment by the test app before the intervention (T1), in which their fitness (Low or High) will be determined. They will then be re-assessed after 4 weeks (T2), after 8 weeks (T3), and after 12 weeks (follow-up T4). The testers will be well trained research assistants who will use their own mobile phone for the testing.

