### Primary outcomes

The primary outcome measures are the changes in the following motor components, all of which are included in the remote fitness assessment (see Table 1 and Additional file 1): static balance (postural control in standing), dynamic balance (postural control while moving), strength (muscle endurance) of upper and lower extremities, and flexibility (range of motion in upper and lower body). All outcomes will be measured among all participants at baseline (T1), at 4 weeks (mid-intervention) (T2), at 8 weeks (end of intervention) (T3), at 12 weeks (one-month post intervention) (T4).

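### The all-participants analysis models pre-intervention T1 as an outcome level, adjusts for neither baseline nor randomisation strata, and names no time point or contrast for the ordered hypothesis

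*Protocol article*

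**What the plan says.** - **Model.** Data analysis in the Protocol article specifies, for each digital marker, "2-ways ANOVAs with repeated measures (3 treatment groups X 4 times measurements", T1 to T4). It is run in all participants, then separately in the four age-by-gender groups, then separately by Low and High fitness on each component. Bonferroni is named for post-hoc tests and the false discovery rate for multiplicity.
- **Status of T1.** In the Intervention section, "all participants will undergo fitness assessment by the test app before the intervention (T1"). T2, T3 and T4 follow at 4, 8 and 12 weeks, the last being one month after the programme ends.
- **Outcome.** Under Primary outcomes, "The primary outcome measures are the changes in the following motor components". All four visits are listed and none is singled out.
- **Hypothesis.** The Background predicts that "participants in the personalized experimental group will show greatest motor improvement in balance, strength, and flexibility", and does so "than participants with similar baseline fitness profiles in the active-control", with the control group changing least.
- **Randomisation.** "We will use permuted block randomization for the following 4 groups", namely two age bands by gender.
- **Power.** Sample size and power analysis gives 86% at f = 0.15 and 99% at f = 0.25 and 0.40 for group differences, and over 99% for the interaction at the two larger effects.

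**The concern.** The hypothesis concerns improvement, ranks three arms and compares people of similar starting fitness. The model chosen for all participants serves it inefficiently in three ways.

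- Randomisation makes the expected group difference at T1 zero. Counting T1 as an outcome level pulls the group main effect towards zero. An effect held constant over T2–T4 is cut to three quarters.
- The group-by-time test spreads 6 degrees of freedom over mid-intervention, end of intervention and one month off programme. It can be significant because the no-intervention arm differs from the other two, even if the personalised programme and WHO advice perform alike.
- The pooled model uses neither the T1 value as a covariate nor the stratification factors. Two arm-lift tests use different weights for women and men (Table 1), so gender is likely to explain variance on those markers.

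At stake is power on each marker if effects are small, and a clear answer on whether the personalised programme beats WHO advice at 8 weeks.

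**Working it through.** **Inputs from the article:** 300 participants, 100 per arm; three groups, four visits; f = 0.15 and 0.25.

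**Assumptions, because the article gives no values:** alpha 0.05; equal variances and one common within-person correlation ρ (compound symmetry), taken as 0.5 and 0.7; equally spaced group means; complete data; one marker without multiplicity correction. The effect at T1, T2 and T3, relative to T3, is 0, 0.5 and 1. At T4 it is 0.5 or 1, which gives the ranges below. Power comes from the noncentral F or t distribution.

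**1. The article's 86%.** Between-groups test averaged over m measures: λ = f²Nm/(1+(m−1)ρ), df 2 and 297.
- m = 4, ρ = 0.5: 0.0225 × 300 × 4/2.5 = 10.8, power 84.2%. With ρ = 0.46 it is 86%.
- m = 5, ρ = 0.5: λ = 11.25, power 85.7%.
- A one-way comparison at a single visit: λ = 6.75, power 63.4%.

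The 86% therefore matches a group main effect in which f applies to the average over all measures.

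**2. Group main effect with T1 null.** λ = f²N·p̄²·4/(1+3ρ), where p̄ is the mean of the profile (0.5 or 0.625).
- ρ = 0.5: 6.75 × 0.25 × 4/2.5 = 2.70, power 29%; 6.75 × 0.3906 × 4/2.5 = 4.22, power 43%.
- ρ = 0.7: λ = 2.18 and 3.40, power 24% and 36%.

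**3. Group-by-time test.** λ = f²N·Σ(p−p̄)²/(1−ρ), df 6 and 891. The sum is 0.5 or 0.6875.
- ρ = 0.5: λ = 6.75 and 9.28, power 45% and 60%.
- ρ = 0.7: λ = 11.25 and 15.47, power 70% and 85%.

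**4. T1-adjusted test at T3.** λ = f²N/(1−ρ²), df 2 and 296.
- ρ = 0.5: 6.75/0.75 = 9.0, power 77%.
- ρ = 0.7: 6.75/0.51 = 13.24, power 91%.
- If the strata explained an assumed 10% of the residual variance, these become 81% and 94%.

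A simulation of 4,000 runs per setting agreed with steps 2 to 4 within about 1.3 percentage points.

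**5. Larger effect.** At f = 0.25, f²N = 18.75. With ρ = 0.5 the interaction has λ = 18.75 or 25.78, power 92% or 98%. The adjusted T3 test has λ = 25.0, power 99.6%.

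**6. Experimental versus active control at T3, f = 0.15.** Means at −d, 0 and d give f² = 2d²/3, so d = 0.15 × √1.5 = 0.184 SD.
- Unadjusted change score, noncentrality d/√(2 × 2(1−ρ)/100): 0.184/√0.02 = 1.30 at ρ = 0.5, power 25%; 0.184/√0.012 = 1.68 at ρ = 0.7, power 39%.
- T1-adjusted, noncentrality d/√(2(1−ρ²)/100): 0.184/√0.015 = 1.50, power 32%; 0.184/√0.0102 = 1.82, power 44%.

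**7. Another profile: effect constant over T2–T4, f = 0.15.**
- ρ = 0.5: main effect 58.5%, interaction 64.7%, T1-adjusted T3 test 76.6%, T1-adjusted mean of T2–T4 95.7%.
- ρ = 0.3: 71.3%, 48.0%, 67.8% and 94.5% in the same order.

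**The case against.** The planned ANOVA is a recognised and valid analysis, and much of the defence stands.

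- **A reader might infer that the plan does not test its hypothesis.** The article does not support that. The primary outcomes are changes, the group-by-time interaction tests whether change differs between arms, and the power section covers that interaction explicitly. Bonferroni post-hoc tests can supply pairwise results. The Low and High fitness analyses address similar starting fitness, though only in two coarse classes.
- **A reader might infer that the strata are ignored.** They are not, since a separate ANOVA is planned in each of the four. What is missing is an adjustment term in the pooled model. Under an additive model, stable differences between people cancel in the interaction, so the omission costs power only in the group main effect.
- **A reader might infer that the fix gives 77% or 91% power for personalised exercise versus WHO advice.** Those figures belong to a 2-df test of any difference among three arms. The pairwise contrast has 32% or 44%, which is below the omnibus interaction's own power. The two answer different questions, so the fair comparator for the contrast is the unadjusted change score.
- **Effect size.** The Abstract ties the sample size to f = 0.25 and 0.40, where little is lost in the test of change.
- **Missed visits.** Classical repeated-measures ANOVA uses complete cases, but the article does not say how incomplete records are treated, and a full plan may. If 5% missed each post-baseline visit independently, 0.95³ = 0.857 would remain, so about 43 of 300 would drop out. Both the rate and the independence are assumptions, so this is an illustration and not a defect shown in the plan.
- **Level of detail.** A fuller plan may add contrasts or covariates. The article nevertheless commits to a two-factor model with T1 as a level, and that choice can be assessed as it stands.

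**Conclusion.** The point holds as a matter of efficiency and specificity, not validity. The all-participants model makes T1 an outcome level, adjusts for neither baseline nor strata, and leaves the ordered hypothesis without a designated time point or contrast.

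For a small effect (f = 0.15) the omnibus cost is material. At ρ = 0.5 the planned tests have 29–43% and 45–60% power against 77% for the adjusted T3 test. At ρ = 0.7 the figures are 24–36%, 70–85% and 91%. At f = 0.25 and ρ = 0.5 the interaction loses only a few points. For the pairwise T3 contrast the gain is modest, 25% to 32% or 39% to 44%, and the fix does not make a small difference between two active programmes easy to detect.

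The sizes depend on the assumed correlation, compound symmetry, effect profile and complete data. The ranking can change: with a constant effect and ρ = 0.3, the diluted main effect (71%) slightly exceeds the adjusted test at T3 alone (68%), although the adjusted T2–T4 mean still does best (94.5%). The change should be made; it is a low-cost improvement, not the repair of an invalid analysis.

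**What to change.** For each marker, in all participants:

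- Fit a linear mixed model with T2, T3 and T4 as outcomes and an unstructured covariance. Fixed effects: group, visit, group by visit, the marker's T1 value and its interaction with visit, age group (65–74, 75+) and gender. Use all available post-baseline data.
- Designate the T3 pairwise contrasts in advance: experimental versus active control first, then experimental versus control and active control versus control. Report T2 and T4 contrasts as supporting results.
- State how the false discovery rate applies across markers to these contrasts, and give power for the first contrast under stated assumptions about correlation and effect profile.
- Keep the planned 3 × 4 repeated-measures ANOVA as a sensitivity analysis. The stratum and Low/High analyses can stay.

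The cost is revised analysis wording and slightly more programming. T1 values, age and gender are already collected or used in randomisation, so no extra participants, visits or measurements are needed.

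### The repeated-measures ANOVA treats the pre-intervention T1 value as a fourth outcome visit instead of a covariate, which costs precision without causing bias

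*Protocol article*

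**What the plan says.** The Data analysis section of the protocol article fixes the model: "2-ways ANOVAs with repeated measures (3 treatment groups X 4 times measurements – T1-T4) will be conducted for each digital marker". It applies this model to all participants, to four age-by-gender subgroups, and to the Low and High fitness levels of each component. It does not say which term (group, or group by time) decides the comparison, and it names no covariate.

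Two other sections establish that T1 is the baseline. Under Intervention, "all participants will undergo fitness assessment by the test app before the intervention (T1"; under Primary outcomes, "All outcomes will be measured among all participants at baseline (T1), at 4 weeks (mid-intervention) (T2". The primary outcomes are defined as changes: "The primary outcome measures are the changes in the following motor components". The hypothesis at the end of the Background is worded conditionally on baseline: the experimental group should improve more "than participants with similar baseline fitness profiles in the active-control".

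The sample size section gives "100 participants in each of the 3 treatment groups (experimental, active control, control", with "statistical power of 86% for a small effect size (Cohen’s f = .15" and "statistical power of 99% for a moderate and high effect sizes (Cohen’s f = .25, .40 respectively". It states neither a correlation between visits nor a significance level.

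**The concern.** A pre-intervention measurement can only be a source of noise or a source of adjustment. As an outcome level it enters the arm comparison in one of two ways.

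- In a group-by-time contrast against T1 it is subtracted in full, so the noise of one short smartphone test is added to every change.
- In the group main effect it is averaged in as a visit at which the expected arm difference is zero.

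As a covariate, T1 would be used only as far as it predicts the later value. The cost of the stated model is wider confidence intervals and lower power than the same data allow, in all 42 marker analyses. The protocol chooses this model itself, so the point does not concern a detail left to an unseen analysis plan.

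**Working it through.** **Inputs.** From the article: three arms of 100 and visits T1 to T4. Assumed: equal variance at each visit (SD = 1), the same correlation rho between any two visits, two-sided 5%, no dropout, and a pairwise difference of 0.3 SD at T3.

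**The plan's own power.** For the between-group term with m visits, lambda = f²·N·m/(1+(m-1)·rho) on 2 and 297 df. With N = 300, m = 4, rho = 0.5 and f = 0.15, power is 84.2%, within 2 points of the stated 86%; rho of about 0.46 gives 86%. At f = 0.25 it is 99.9%. A one-way ANOVA without repeated measures gives 63.4% at f = 0.15, so the stated figure is a repeated-measures group main effect. Four visits at rho near 0.5 fit it, which suggests that T1 was counted. This is not proof, because three visits at rho = 0.4 give 85.7%. The interaction (lambda = f²·N·m/(1-rho), 6 and 891 df) exceeds 99.9% at f = 0.25 and 0.40, so the stated interaction power is also reproduced.

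**If the arm effect is read from group by time.** The contrast at T3 against T1 is a difference in change scores.

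- Variance per participant, change: 2(1-rho).
- Variance per participant, T1 as covariate: 1-rho².
- Ratio, covariate to change: (1+rho)/2, so the share saved is (1-rho)/2.
- Standard error of an arm contrast: sqrt(2·variance/100); power by normal approximation.

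| rho | variance, change | variance, covariate | share saved | power at 0.3 SD, change | power at 0.3 SD, covariate |
|---|---|---|---|---|---|
| 0.3 | 1.40 | 0.91 | 35% | 43% | 60% |
| 0.5 | 1.00 | 0.75 | 25% | 56% | 69% |
| 0.7 | 0.60 | 0.51 | 15% | 78% | 84% |
| 0.8 | 0.40 | 0.36 | 10% | 92% | 94% |
| 0.9 | 0.20 | 0.19 | 5% | 99.7% | 99.8% |

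At rho = 0.5 the standard error falls from 0.141 to 0.122 SD. The covariate model would then need 75 per arm for the precision that the change score gets from 100. A simulation of 20,000 trials at rho = 0.5 gave standard errors of 0.142 and 0.123.

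**If the arm effect is read from the group main effect.** With no expected arm difference at T1 and a constant effect at T2 to T4, the four-visit mean carries 3/4 = 0.75 of the effect. At rho = 0.5 its variance is (1+3·0.5)/4 = 0.625, so signal per SD is 0.75/sqrt(0.625) = 0.95. For the T2-T4 mean adjusted for T1, the variance is (1+2·0.5)/3 - 0.5² = 0.417 and signal per SD is 1/sqrt(0.417) = 1.55. At rho = 0.8 the two figures are 0.81 and 2.10, so on this reading a high correlation does not shrink the loss.

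**The same loss seen through baseline imbalance.** Given an observed T1 difference between two arms, the change contrast moves by -(1-rho) times that difference. The excess variance is 2(1-rho) - (1-rho²) = (1-rho)², which is exactly the variance of that movement on the same per-participant scale. In the simulation, the slope of the estimate on the T1 difference was -0.496 for change and 0.004 with the covariate, and both estimators averaged 0.000.

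**The case against.** The strongest reply is that nothing here is invalid. Over randomisation the change contrast is unbiased, and it directly addresses an outcome that the article defines as change. That stands. A reader might infer that chance T1 differences bias the trial, especially as 42 markers and three arm pairs give 126 baseline comparisons, of which 126 × 0.05 = 6.3 would be expected at p < 0.05. The documents do not support a bias claim. The movement is conditional on the realised imbalance, it averages to zero, and it is the precision loss already counted. Stratification by age and gender would also reduce imbalance on markers related to either.

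A second reply is that conditioning on baseline is already planned, through the separate Low and High fitness analyses with levels set at T1. These do address the hypothesis about similar baseline profiles, so it would be wrong to say that the plan ignores it. But two levels condition only coarsely, and they do nothing for the all-participants analysis.

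Third, the size of the change-score loss is uncertain. The article gives no rho, the gain is small at 0.8 or above, and 0.3 SD is not the protocol's target. No stated power figure is shown to fail.

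Finally, a reader might extend the criticism to mood and cognition. The article says only that these are compared between groups and fixes no model for them, so there is nothing to correct.

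**Conclusion.** The point holds as an avoidable loss of precision, not as an error or a bias. The model's treatment of T1 is explicit, and both possible readings of the arm effect are affected. For a change contrast at one visit, adjustment would save 35% of the variance at rho 0.3, 25% at 0.5, 15% at 0.7, 10% at 0.8 and 5% at 0.9. For the group main effect, a constant post-baseline effect is diluted to 0.75. The direction is certain in samples of this size. The amount rests on the assumed rho, equal variances and equal correlations, and the power figures also rest on the assumed 0.3 SD difference. It cannot be said that the plan estimates every arm effect as a change score, because the deciding term is not named and the stated power for group differences matches a main effect.

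**What to change.** In Data analysis, make T2, T3 and T4 the outcome visits. Enter the T1 value of the same marker as a covariate, with a T1-by-visit term. Read the arm effect at each visit, with T3 as the end of intervention, and say so. Use the same model within the age-by-gender and fitness-level subgroups. The outcome may still be expressed as change from T1: with T1 as covariate, change and follow-up value give the same arm effect, so the Primary outcomes section need not be altered. A longitudinal model that keeps T1 but constrains its mean to be equal across arms would also serve.

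The cost is analysis wording and a few degrees of freedom (one for T1 and two for T1 by visit). No new data are needed, because T1 is already collected from everyone to set the fitness level.

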## Measurements

### Remote fitness assessment tool

We will use standard movement performance tests selected by experts and incorporated into the smartphone application (EncephaLog™) developed by Montfort Brain Monitor LTD, utilizing the standard smartphone sensors - accelerometers and gyroscopes. The assessment will include 10 performance tests, operationalized to generate a total of 42 digital markers (see Table 1 and Additional file 1). Briefly, the 10 performance tests assess the following fitness components: static balance, dynamic balance, leg strength, upper body flexibility, and upper extremities strength. Raw data will be uploaded to the remote pooled databank. An example showing graphical demonstration of the raw data collection for the “one-leg stance” is presented in Fig. 4.

**Table 1 Tab1:** Outcome measures

Fitness Components	Tests	Digital Markers	Good performance
Static balance	^a^One-leg stance 10 s.	For each test: average acceleration (m/sec^2^) and angular velocity (radians/sec), in different directions.	*Lower scores – lower sway*
	^a^Tandem stance 20 s.		
Dynamic balance	Tandem walk: 10 steps forwards		
	Tandem walk: 10 steps backwards		
Legs strength	Sit-to-stand 10 rep.	Total time (sec.) and average duration for each rep.	*Shorter duration*
Upper body flexibility	^a^Torso rotation	Angle	*Increased angle - a greater range of motion*
	^a^Arm flexion		
	^a^Arm extension		
Upper extremities strength	^ab^Lifting arm forward 20 rep.	Average duration (sec.)	*Shorter duration*
	^ab^Lifting arm to side 20 rep.		

^a^For left and right separately

^b^with 0.5 kg for women and 1 kg for men

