### Secondary outcomes

Adherence to the exercise programs and changes in feelings and cognition will be compared between the different study groups. In addition, age (65-74 vs 75+) and gender differences in the changes in the primary outcomes will be examined, as well as levels of fitness (Low vs High).

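### The secondary question about age, gender and fitness-level differences is analysed only by separate ANOVAs within each subgroup, and none of these tests a difference between subgroups

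*Protocol article*

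**What the plan says.** Under Secondary outcomes, the protocol article names differences between two age bands, divided at 75, and adds that "gender differences in the changes in the primary outcomes will be examined, as well as levels of fitness (Low vs High"). This asks whether the changes differ from one subgroup to another.

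The Data analysis section names the model, "2-ways ANOVAs with repeated measures (3 treatment groups X 4 times measurements", T1 to T4), for each digital marker. It is run on all participants, then separately for "each of the following four subgroups: young women and young men (age 65-74), and old women and old men (age 75" and over), then "Separately for each of the two levels of fitness (Low and High) for each component". On multiplicity it says "Bonferroni will be used for post-hoc analyses, and False Discovery Rate" will account for multiple comparisons.

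Two other sections bear on this. The Randomization section uses permuted blocks within the same four age-by-sex groups. The Intervention section and the section on matching fitness level with exercise prescription set Low or High from the T1 assessment, for each component, by a system built on pilot data.

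**The concern.** Whether a treatment effect differs between two subgroups is a question about the difference of two effects. A group x time test inside one subgroup asks only whether the arms diverge there. If that test is significant in younger women and not in older men, nothing has been tested about younger women against older men. The two estimates may be almost equal, with one falling just short of the threshold.

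No planned model contains age, sex or fitness level, so the secondary question has no test. Bonferroni and False Discovery Rate adjust the p-values of the within-subgroup tests; they do not supply the missing comparison. What is at stake is a claim that personalization works in one age, sex or fitness group and not in another, when the data do not show it. There are many chances for such a claim: 42 markers x (4 + 2) subgroup ANOVAs = 252.

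**Working it through.** **Inputs.** From the article: "100 participants in each of the 3 treatment groups (experimental, active control, control"), so N = 300; k = 3 arms; m = 4 visits; effect sizes f = 0.15, 0.25 and 0.40. Not stated, so assumed: alpha 0.05; correlation between visits rho = 0.5 (0.7 and 0.8 also shown); equal cells, 300/4 = 75 per age-by-sex cell and 300/2 = 150 per fitness level; no dropout; sphericity; unadjusted tests. The value f = 0.10 is added to show the curve.

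**1. The plan's own power figure.** For the repeated-measures test between groups, lambda = N m f² / (1 + (m - 1) rho), with 2 and 297 df. At f = 0.15 and rho = 0.5: 300 x 4 x 0.0225 / 2.5 = 10.8, power 84.2%. At rho = 0.45: 27 / 2.35 = 11.49, power 86.5%. The stated 86% is therefore reproduced with rho a little under 0.5, which makes 0.5 a reasonable working value. At f = 0.25, lambda = 30 and power is 99.9%, in line with the stated 99%. These figures are for the whole sample.

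**2. Power of group x time inside one cell of 75.** lambda = 75 x 4 x f² / (1 - rho), with (3 - 1)(4 - 1) = 6 and 3 x (75 - 3) = 216 df. At rho = 0.5:
- f = 0.10: lambda = 6.0, power 39.1%
- f = 0.15: lambda = 13.5, power 78.2%
- f = 0.25: lambda = 37.5, power 99.9%

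**3. Chance of a mixed pattern when the true effect is the same in all four cells.** This is 1 - p⁴ - (1 - p)⁴, where p is the power in one cell. At f = 0.15 and rho = 0.5: 1 - 0.374 - 0.002 = 0.624.

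| Common effect | rho 0.5 | rho 0.7 | rho 0.8 |
|---|---|---|---|
| none (p = 0.05) | 18.5% | 18.5% | 18.5% |
| f = 0.10 | 84% | 82% | 52% |
| f = 0.15 | 62% | 15% | 1.3% |
| f = 0.25 | 0.5% | under 0.1% | under 0.1% |

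The chance exceeds 50% only when power in a cell lies between about 16% and 84%. At rho = 0.5 that means f of about 0.06 to 0.16. A higher correlation moves this band to smaller effects: at f = 0.05 the chance rises from 39% (rho 0.5) to 53% (rho 0.7). With unequal cells of 120, 90, 54 and 36 (an assumption) and rho = 0.5, it is 79% at f = 0.15 and 12.5% at f = 0.25.

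**4. Two fitness levels.** With equal power the chance is 2p(1 - p), which peaks at 50% when p = 0.5. With 150 per level and rho = 0.5 it is 39% at f = 0.10 (p = 73.1%), 3% at f = 0.15 (p = 98.6%) and about 0% at f = 0.25.

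**5. One model instead.** In 4,000 simulated trials per effect size (25 per arm per cell, rho = 0.5), a group x time x four-cell interaction test falsely declared a difference in 4.5% to 5.2% of trials for common effects from f = 0 to 0.25. In the same trials the separate ANOVAs gave a mixed pattern in 17.6% (f = 0), 84.2% (0.10), 61.7% (0.15) and 0.5% (0.25).

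**The case against.** Several objections carry weight.

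- *The within-cell comparisons are legitimate.* Randomization is blocked within the age-by-sex cells, so arms can be compared fairly inside each. The study hypothesis also concerns participants with similar baseline fitness. This stands: the separate ANOVAs answer a valid question and can be kept. They do not answer the one under Secondary outcomes.
- *No rule is stated for reading significant here and not significant there as a difference.* True. A reader might infer that the plan commits to that rule, and it does not. But it offers no other route from the listed analyses to the stated question.
- *The separate tests will not usually mislead.* A reader might infer that they will. The figures do not support this: 18.5% with no effect, 0.5% at f = 0.25 for group x time, and never above 50% for two equally powered fitness levels. The False Discovery Rate adjustment would also change every percentage.
- *Regression to the mean.* T1 helps define Low and High and is also the first outcome visit, so the Low group may improve over time without treatment. A reader might infer that this biases the treatment comparison. It does not: randomized arms share it in expectation, and the plan's own example compares arms within a level. Its size cannot be derived, because Low/High is set per component by a system built on pilot data, not by a described split on the marker analysed.
- *An unseen analysis plan may add interaction tests.* It may. But the article goes beyond silence: it fixes the factors, visits and subgroups, and that model lacks the term needed.

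**Conclusion.** The point holds in this form: the plan asks about differences between subgroups and fixes only analyses within subgroups. That mismatch follows from the text and depends on no assumed number.

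The practical risk depends on the common effect size. For the four age-by-sex cells, the chance of a spurious mixed pattern on group x time runs from near zero to about 84% under the assumptions above. It is 62% at the plan's own small effect (f = 0.15) with rho = 0.5, falling to 15% and 1.3% at rho 0.7 and 0.8. At the plan's moderate effect (f = 0.25) with equal cells it is 0.5% or less. The documents do not support a claim that false subgroup differences are the usual result, that the within-cell comparisons are invalid, or that the between-arm contrast within Low or High is biased. This concerns a secondary analysis and should be corrected before the data are analysed.

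**What to change.** For each marker, fit one model on all participants that includes the age-by-sex randomization stratum. Test group x time x age group, group x time x sex, and group x time x baseline fitness level. Use Low/High for the component to which the marker belongs, since that level also sets the exercise difficulty assigned; the continuous T1 value may be added as a second form.

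Report each subgroup's treatment effect with a confidence interval from this model, beside the interaction p-value, and label the results exploratory. Keep the separate-cell ANOVAs as description only. State that the change over time within Low or High will not be read as benefit, because regression to the mean would appear in every arm.

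The cost is a change of analysis wording, with no effect on recruitment, visits or measurements. There are three interaction tests per marker in place of six subgroup ANOVAs (126 against 252 over 42 markers). The downside is that interaction estimates will have wide confidence intervals, and the article should say so.
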